# Routine Physical Therapy

Physical therapy is popular in the treatment of patients with cerebral palsy. The purpose is to maintain the range of motion and muscle strength to maintain or improve it. Physical therapy can also help improve walking.

The physical therapy in this study was performed by a physical therapist with 5 years of experience (with a certificate in pathology) for a total of 6 weeks, 3 times a week for 40 minutes each time, for a total of 120 minutes/week, each time consisting of stretching exercise for 10 minutes, strengthening exercise for 15 minutes, and ambulatory training for 15 minutes. Stretching exercise and strength training will be selected according to specific affected muscle of each participant for safety e.g. gastrosoleus complex, tibialis posterior, peroneal muscle, rectus femoris, hamstring, hip adductor muscle, iliopsoas muscle, biceps brachaii.

# Home Program Physical Therapy

Participants or their parents will be taught physical therapy at home by doing it 5 times/week for at least 30 minutes each time, for a total of 150 minutes/week. The patient performs shoulder abduction/flexion, elbow flexion/extension, hip extension/abduction, and knee extension/flexion in repetitive movements for 3-5 minutes on both sides, and ambulatory training is the practice of moving both arms and legs forward, backward, left and right (side-to-side). Gait aid is allowed if available.

# Washout Period

This study set a washout period of 6 weeks, based on a study by Esin-Yi Kathy Cheng et al.^20^ that conducted a cross over randomized controlled trial using a 6-week washout period in children with cerebral palsy who were treated with whole body vibration versus physical therapy, and inferred from the literature that studied muscle spasms after a stroke. It was found that the patient began to have muscle stiffness at 6 weeks.^21^

By 6 weeks during the washout period, patients can still use walking aids/splints, plastics, or take their own medications as usual. However, they cannot receive other additional treatments (co-intervention) such as botulinum A toxin injections, physical therapy or any additional massage, additional surgery to correct muscle spasms, etc. There will be a follow-up phone call to inquire about the symptoms and whether they have received other treatments every 2 weeks. In case the temperature of the study participant is more than 38.0 degrees Celsius. Patients will not be able to undergo visual therapy, including Thai traditional massage. Patients can receive treatment in the next week or sooner. If the patient has a fever for more than 1 week and the cause cannot be determined, or the fever that requires a long treatment time, such as cancer, leukemia, malaria, pulmonary tuberculosis, etc., it will be necessary to withdraw from the research. However, the data of patients participating in the research will remain in the analysis.

Since the home program will start from the beginning of the first step analysis to the end of the experiment by the participants themselves or their parents will assist in doing it, during the washout period, the participants will be asked to do the home program like the period when they are treated with Thai massage or physical therapy according to the method specified above.

# Gait analysis

The steps of the gait analysis are as follows:

1. Wear a comfortable outfit to attach the movement measuring instrument and electromyography to the skin.

2. Attach a total of 29 motion capture devices according to Helen Hayes’ method.

3. Electromyography devices were attached using bipolar Ag/AgCl electrodes (3M Red dot, size 35 × 40 cm) on the skin at various locations including hip muscles, rectus femoris muscles, hamstring muscles, anterior tibial muscles, and posterior calf muscles.

4. Wear a device to measure oxygen consumption using the Oxycon mobile by CareFusion from Germany.

5. Measure the maximum voluntary contraction of each muscle group as mentioned above. To be used as the basis for individual analysis using ProEMG software, Myon 320 wireless EMG (Myon AG, Schwarzenberg Switzerland).

6. The participants were asked to walk in a straight line for about 8 meters for 10-15 laps with the same gait pattern. Measured by 3D motion capture and Coretex 6.2 software, data analysis with OrthoTRack 6.61 (Motion Analysis Corporation, Santa Rosa, CA, USA) and measurement of electromyography while walking. Select the 3 best rounds to calculate the kinematics and kinematics of the joints (in case it is not possible to attach both devices at the same time, each device will be separately installed and measured).

7. Participants were asked to stand and walk on a pedobarograph to measure their foot preference while standing and walking using the Sensor Medica Pedobarograph (Rome, Italy).

[figure not shown]

[figure not shown]

[figure not shown]

[figure not shown]

[figure not shown]

[figure not shown]

[figure not shown]

[figure not shown]

[figure not shown]

[figure not shown]

**Figure 3** 3D gait analysis equipment

| Research Schedule | Jul. 21 – Jul. 22 | Jul. 22 – Feb. 23 | Feb. 23 – May. 23 |
| --- | --- | --- | --- |
| Subject recruitment & operation |  |  |  |
| Data collection |  |  |  |
| Data analysis |  |  |  |

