**Table 1** Massage Patterns and Duration ^11-15^

[figure not shown]

**Table 2** Research methodology and results of massage ^11-15^

[figure not shown]

Reducing gait disorders caused by muscle spasm is another goal of treating the disease. Therefore, measuring the effect of massage on walking using a 3D gait analysis is another effective method. Because a large amount of quantitative data is collected during the test to increase the accuracy of analysis and evaluation of gait performance and reduce systematic error by displaying various forms of results such as temporal spatial, kinetics, kinematics, electromyography data, etc.^16^

This is because gait analyzers can provide large amounts of data, and they are quite complex. At present, representatives of such datasets have been invented for easy communication, such as the Gillette Gait Index (GGI), Gait Deviation Index (GDI), Gait Profile Score (GPS), etc^17^. The study found GPS represents the most useful dataset because no large reference dataset is required. GPS is calculated from 9 sets of Gait Variable Scores (GVS) combined to provide an overview of all walks. While GVS represents kinematics data comprises 9 sets of Pelvic tilt, Hip flexion/ extension, Knee flexion/ extension, Ankle dorsiflexion/ plantar flexion, Pelvic obliquity, Hip abduction / adduction, Pelvic rotation, Hip internal/ external rotation and Foot progression angle. GVS is calculated as the square root of the mean of the difference between the walker's kinematics data and the person's normal value (Averaged Normative Reference Dataset) squared, also known as Root Mean Square Error (RMSE). Therefore, the factors that affect GPS includes pelvic tilt and rotation, ability to flex/extend/rotate/adduct/abduct the hips, ability to flex/extend the knee, ability to dorsiflex/plantarflex the ankle. The higher GPS, the more gait abnomality.^17^

If there is precise processing, create a good research protocol to clearly define the duration of the experiment and the sample, it will lead to a very accurate description of the effect of massage on muscle tension that affects the gait of patients with cerebral palsy. Although the results did not differ between massage and physical therapy. If there were significant differences within the intervention group, Thai massage may also be another non-surgical treatment option and is considered to support Thai wisdom in the treatment of diseases.

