# Objectives of the research project

To study and compare the effects of traditional Thai massage with regular physical therapy. In the development of gait in patients with spasticity, it was evaluated from the gait profile score.

- Primary outcome: Gait profile score (GPS)
- Secondary outcome: Modified Ashworth Scale, Temporal spatial data, Kinetics data, Oxygen consumption, Electromyography and Pedobarography

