# Specify the number of research participants (Subject) to be studied, along with the entry and exclusion criteria.

Reference from mean GPS (Rasmussen HM, Nielsen DB, Pedersen NW, Overgaard S, Holsgaard-Larsen A. Gait Deviation Index, Gait Profile Score and Gait Variable Score in children with spastic cerebral palsy: Intra-rater reliability and agreement across two repeated sessions. Gait Posture. 2015; 42(2):133-7)

Use programmatic calculations STATA 16.0, Stata Corp, College Station, Texas, USA to estimate the sample size of difference two independent mean test due to a randomized controlled trial. Configure the variables as follows:

- Based on Alpha error 0.05 and power of the study 0.8

- Mean Gait Profile Score (GPS) of spastic cerebral palsy in the control group 13.90

- The difference in the mean Gait Profile Score (GPS) between the experimental group and the control group for the alternate hypothesis was 20 percent or 11.12.

- The standard deviation of the Gait Profile Score (GPS) of the control group was 4.9.

- Standard deviation of the Gait Profile Score (GPS) of the experimental group valued at 1.3

The sample size was calculated for each group of 26 cases.

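### The primary gait score comes from the 3 best of 10 to 15 laps, with no criterion for best and no masking of the selector stated, so it is open to outcome-dependent selection

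*Protocol*

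**What the plan says.** The Objectives section names GPS as the only primary outcome. The Introduction explains how it is built: "GPS is calculated from 9 sets of Gait Variable Scores (GVS) combined to provide an overview of all walks". Each component is the root-mean-square distance of a kinematic curve from a normal reference, and a larger score is worse: "The higher GPS, the more gait abnomality". Whatever laps supply the kinematics therefore supply the primary endpoint.

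Step 6 of the Gait analysis section fixes those laps. Participants are to "walk in a straight line for about 8 meters for 10-15 laps with the same gait pattern", and the instruction is then "Select the 3 best rounds to calculate the kinematics and kinematics of the joints". The research plan repeats the gait analysis four times, before and after each treatment period.

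The visible text does not say what makes a lap best, who decides, how many laps within the 10 to 15 are walked at a given session, or whether the person deciding is masked. The flow figures are not reproduced in the available text.

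**The concern.** The comparison is of massage with physiotherapy in a crossover. Participants and therapists cannot be masked to it, so the protection of the primary result lies in how the gait recordings are processed. At that step the protocol sets a rule that turns on an undefined judgement and leaves 7 to 12 of the laps walked out of the calculation.

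On one reading, the laps are picked because the walking in them looks best. GPS then describes the favourable end of a participant's performance, and how favourable depends on how many laps were available and how variable they were. On another reading, the laps are picked because the recording is cleanest. That is harmless if gait quality plays no part, but without a written criterion the choice cannot be reproduced or audited. On either reading, a selector who knew the treatment or visit would have room to lean. What is at stake is the massage-physiotherapy difference in GPS.

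**Working it through.** **Inputs from the protocol.** Laps per session: 10 to 15. Laps used: 3. Control mean GPS 13.90 and experimental mean 11.12 (sample size section), so the planned difference is 13.90 − 11.12 = 2.78, which is 20% of 13.90. Planning SDs: 4.9 and 1.3.

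**Assumed input.** The protocol gives no lap-to-lap SD within a session. Call it *s*; the range 0.5 to 1.5 degrees is an assumption.

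**The plan's own figure.** With a two-sided 0.05 test and power 0.80, n = (1.960 + 0.842)² × (4.9² + 1.3²) / 2.78² = 26.1 per group, against the stated 26. The lap rule does not change that figure; 2.78 serves below only as a yardstick.

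**Shift in one session's GPS if best means least deviant.** Treat the lap scores of a session as independent normal values around the session mean. The expected shift is *s* times the mean of the three lowest of *m* standard normal values, estimated from 400,000 simulated sessions:

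| Laps *m* | Shift | *s* = 0.5 | *s* = 1.0 | *s* = 1.5 |
|---|---|---|---|---|
| 10 | −1.064 *s* | −0.53 | −1.06 | −1.60 |
| 12 | −1.179 *s* | −0.59 | −1.18 | −1.77 |
| 15 | −1.310 *s* | −0.66 | −1.31 | −1.97 |

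These are shifts in the level of GPS. If the shift is the same in every session, it cancels when massage is compared with physiotherapy.

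**What does not cancel.** Three routes lead to bias in the contrast:

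1. *Lap count.* At the extreme, every session under one treatment has 10 laps and every session under the other has 15. The difference is (1.310 − 1.064) *s* = 0.246 *s*, or 0.12 to 0.37 degrees for *s* of 0.5 to 1.5, which is 4% to 13% of 2.78. Spread over five laps this is about 0.05 *s* per lap. An average imbalance of one lap gives about 0.025 to 0.075 degrees, 1% to 3% of 2.78.
2. *Lap variability.* Suppose one treatment lowers *s* from 1.0 to 0.5 (assumed). The shift changes by 1.064 × 0.5 = 0.53 (10 laps) to 1.310 × 0.5 = 0.66 (15 laps), or 19% to 24% of 2.78. The treatment that made gait steadier would gain less from the selection and so look worse.
3. *The selector's choices.* Suppose the least deviant laps are taken under one treatment and typical laps under the other. At an assumed *s* of 1.0 the difference is 1.06 to 1.31 degrees, or 38% to 47% of 2.78. This is a limiting case and not a forecast.

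**If best means technically cleanest.** When the choice is unrelated to gait quality, the expected shift is zero for any number of laps, and the first two routes vanish.

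**The case against.** The protocol never says that laps are chosen by their GPS or by how good the gait looks. It asks for a uniform gait pattern across laps, and in a translated text best may simply mean best recorded. This stands: outcome-dependent selection is something the wording allows, not something it prescribes.

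A reader might also infer that the selector knows the treatment. The documents do not support that as a fact. The visible text is silent and the flow figures are missing. The first gait analysis is listed ahead of random assignment, so the worry is weaker at baseline.

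The strongest temptation is to set the level shift of 0.5 to 2.0 degrees beside the planned 2.78 and conclude that most of the effect could be artefact. That comparison is wrong, because a shift in level is not a shift in a treatment difference. Of the quantities in the table, only differences between treatments or visits matter, and nothing in the protocol suggests that lap count follows treatment.

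Nor does the Introduction's remark that GPS gives an overview of all walks promise that every lap is used. It describes combining nine joint and pelvic measures into one score.

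The loss of precision is minor. The sampling SD is about 0.41 *s* for the best 3 of 12 and 0.29 *s* for the mean of all 12. The extra variance of about 0.08 *s*² is at most 0.19 at *s* = 1.5. The average planning variance is (4.9² + 1.3²)/2 = 12.85, so this is about 1.5%. The within-person variance that a crossover would use is not given.

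Finally, such detail might be left to a statistical analysis plan, which is not available here. But the protocol does not leave this point open: it writes a working rule for the primary endpoint, and the rule rests on an undefined word.

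**Conclusion.** The point holds in a conditional form and should be fixed. The protocol bases its sole primary outcome on a subjective pick of 3 laps from a variable 10 to 15, with no criterion and no stated masking, in a comparison whose treatments cannot be masked. That leaves GPS open to outcome-dependent selection; it does not show that such selection will occur.

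If best means least deviant gait, session GPS falls by about 1.06 to 1.31 lap SDs. The treatment contrast is biased only through differences between treatments or visits. The lap-count route is small, at most 0.25 lap SD. Lap variability and the selector's choices could matter more, but their size is not known from the protocol. If best means cleanest recording, judged without regard to gait, no such bias need arise.

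The figures assume a lap SD of 0.5 to 1.5 degrees and independent normal lap scores averaged into GPS. The protocol does not say whether GPS is averaged over laps or computed from averaged curves, so they are approximate. The sample size is unaffected.

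**What to change.** In step 6, replace the selection of the 3 best laps with all technically valid laps. Define validity in advance, for example no marker drop-out and a complete gait cycle. If exactly three laps are needed, take the first three valid ones in recording order. Accept or reject laps on files stripped of treatment, sequence and visit labels. Someone who attended the session may still recognise it, so a colleague who was not present is the better choice where available. The rule should be in place before any laps are selected.

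With a rule unrelated to the gait result, the expected selection shift is zero. Using all valid laps is the better option: the mean of any three has a sampling SD of *s*/√3 = 0.58 *s*, against 0.29 *s* for all 12.

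The cost is some extra processing of laps already recorded, plus coding of the files. No new assessments are needed. Absolute GPS values may be higher than under best-of selection, which matters when they are compared with values obtained that way.

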# Protocol Flow Chart

**
[figure not shown]
**

**Figure 4** CONSORT DIAGRAM

# Specify the number of research participants (Subject) to be studied, along with the entry and exclusion criteria.

Reference from mean GPS (Rasmussen HM, Nielsen DB, Pedersen NW, Overgaard S, Holsgaard-Larsen A. Gait Deviation Index, Gait Profile Score and Gait Variable Score in children with spastic cerebral palsy: Intra-rater reliability and agreement across two repeated sessions. Gait Posture. 2015; 42(2):133-7)

Use programmatic calculations STATA 16.0, Stata Corp, College Station, Texas, USA to estimate the sample size of difference two independent mean test due to a randomized controlled trial. Configure the variables as follows:

- Based on Alpha error 0.05 and power of the study 0.8

- Mean Gait Profile Score (GPS) of spastic cerebral palsy in the control group 13.90

- The difference in the mean Gait Profile Score (GPS) between the experimental group and the control group for the alternate hypothesis was 20 percent or 11.12.

- The standard deviation of the Gait Profile Score (GPS) of the control group was 4.9.

- Standard deviation of the Gait Profile Score (GPS) of the experimental group valued at 1.3

The sample size was calculated for each group of 26 cases.

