# Research Methods and Research Patterns Research Schedule

Research Model: Crossover randomized controlled trial

- Patients who meet the criteria and agree to participate in the research will be interviewed and examined to collect basic information and make an appointment for gait analysis.

- Participants will be analyzed by motion capture machine from Motion analysis corporation, Santa Rosa, CA, USA and recorded using Cortex 6.2 program. Data will be analyzed using Orthotrak and participants will be randomly assigned to group A and B.

- Participants will be taught home program physical therapy and will be taught from the beginning of the study to the end of the study for 18 weeks.

- Group A will receive traditional Thai massage according to the regulations mentioned above for 6 weeks, and then will be analyzed for a second time.

- Group B will receive regular physical therapy for 6 weeks, then will undergo a second walking analysis.

- Once Group A or B has undergone a second gait analysis, a 6-week interval will be given.

- Once the third gait analysis is undertaken, treatment will be alternated where group A will receive physical therapy as usual. Group B will receive a traditional Thai massage for 6 weeks.

- Both groups will then be analyzed for a fourth time.

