# In case the sample size increases by 20 percent, the total sample size is 32 cases per group.

**Inclusion Criteria**

1. Patients with spastic cerebral palsy
2. Age over 5 years
3. Gross Motor Function Classification System (GMFCS) levels I to III (Figs. 2 and 3)
4. Agree to participate in the research project by signing

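### The sample size is calculated for two independent groups, but the trial is a two-period crossover, so 26 per group at 80% power does not describe its own comparison

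*Protocol*

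**What the plan says.** The Protocol's section on research methods and schedule states the design as "Research Model: Crossover randomized controlled trial". Group A has massage for 6 weeks and group B physical therapy. After a 6-week interval the groups exchange: "treatment will be alternated where group A will receive physical therapy as usual. Group B will receive a traditional Thai massage for 6 weeks". Gait is analysed four times, before and after each treatment period. The washout section confirms the interval: "This study set a washout period of 6 weeks". The primary outcome is the Gait Profile Score (GPS).

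The section on the number of participants uses a two-sample calculation, run "to estimate the sample size of difference two independent mean test due to a randomized controlled trial". The inputs are "Based on Alpha error 0.05 and power of the study 0.8"; "Mean Gait Profile Score (GPS) of spastic cerebral palsy in the control group 13.90"; a 20 percent effect; and SDs of 4.9 (control) and 1.3 (experimental). The result is 26 per group. The line just above the inclusion criteria adds 20 percent, after which "the total sample size is 32 cases per group".

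Neither place gives a within-participant SD or a correlation between periods. Neither says that only the first period is compared, or that a parallel-group size was kept on purpose.

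**The concern.** The reason given for the two-sample formula is that the trial is randomised. Randomisation does not make the two treatment samples independent when the same people supply both. In a crossover the treatment effect is estimated within participants, and its precision depends on the SD of the paired difference and on the total number randomised. The two-sample formula uses neither: it takes two between-participant SDs and counts each person under one treatment only.

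The stated size and power therefore belong to a comparison of two separate groups, each measured once. A reader cannot tell from the protocol what power the planned enrolment gives for the comparison the design was built for, or what difference it can detect. That matters because the sample size justifies asking participants from childhood upward for 18 weeks and four gait analyses.

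**Working it through.** **Inputs from the protocol.** Alpha 0.05, power 0.80, control mean 13.90, SDs 4.9 and 1.3. The effect is 0.20 x 13.90 = 2.78. The 11.12 printed beside it is the resulting experimental mean, 13.90 - 2.78. Sidedness is not stated; two-sided is used because it reproduces the protocol's figure.

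**Step 1: reproduce the stated figure.** Two independent means, normal approximation:

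n per group = (1.960 + 0.842)^2 x (4.9^2 + 1.3^2) / 2.78^2 = 7.849 x 25.70 / 7.728 = 26.1.

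This is the protocol's 26 (one-sided would give 21). Inflation: 26 x 1.2 = 31.2, rounded up to 32. The totals are 52 and 64.

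**Step 2: the crossover contrast.** With balanced sequences, the treatment effect adjusted for period has variance SD_diff^2 / N, where N is the total over both sequences and

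SD_diff = sqrt(SD1^2 + SD2^2 - 2 x r x SD1 x SD2).

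Power comes from a noncentral t with N - 2 degrees of freedom and noncentrality 2.78 x sqrt(N) / SD_diff. The protocol gives no r, so r is assumed over a range. At r = 0 the normal-approximation formula of Step 1 returns the same 26.1, but as the total number of participants and not the number per group.

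**Step 3: direct contrast of the two treatments.** The detectable difference (80% power) is proportional to SD_diff. A difference of 2.78 corresponds to SD_diff 7.02 at N = 52 and 7.81 at N = 64, so it equals 2.78 x SD_diff / 7.02 or 2.78 x SD_diff / 7.81.

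| SDs | r | SD_diff | Total N for 80% | Power at 52 | Power at 64 | Detectable at 52 / 64 |
|---|---|---|---|---|---|---|
| 4.9 and 1.3 (protocol) | 0 | 5.07 | 29 | 97% | 99% | 2.01 / 1.80 |
| | 0.5 | 4.40 | 22 | 99.4% | 99.9% | 1.74 / 1.56 |
| | 0.8 | 3.94 | 18 | 99.9% | >99.9% | 1.56 / 1.40 |
| 4.9 under both (assumed) | 0 | 6.93 | 51 | 81% | 88% | 2.75 / 2.47 |
| | 0.5 | 4.90 | 27 | 98% | 99% | 1.94 / 1.74 |
| | 0.8 | 3.10 | 13 | >99.9% | >99.9% | 1.23 / 1.10 |

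For 52 participants to give exactly 80% power, SD_diff would have to be about 7.0. The protocol's own SDs imply at most 5.07 for r of 0 or more.

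**Step 4: contrast of changes from each period's own baseline.** Four gait analyses make this possible. Assume SD 4.9 at every visit and the same correlation r between any two visits. Then SD_diff = 2 x 4.9 x sqrt(1 - r).

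- r = 0.3: SD_diff = 9.8 x 0.837 = 8.20; total N for 80% = 71; power 67% at 52 and 76% at 64 (noncentrality at 64 = 2.78 x 8 / 8.20 = 2.71).
- r = 0.5: SD_diff = 9.8 x 0.707 = 6.93; total N = 51; power 81% at 52 and 88% at 64.
- r = 0.7: SD_diff = 5.37; total N = 32; power 96% at 52.

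The answer depends on which contrast is primary and on an r that the protocol does not give.

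**The case against.** The strongest reply is that nothing in the conduct has to change. The two-sample formula was applied correctly. For a direct contrast with non-negative correlation it gives more power than declared, and sizing a crossover as if it were parallel is a recognisable conservative habit. It would also be the right formula if only first-period data were used, for instance because of carryover. Much of this stands: the fault is a mismatch of method and design, it is not an arithmetic error, and it does not by itself weaken the primary comparison. But the protocol claims neither defence, and neither can be read into its stated reason, which is only that the trial is randomised.

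It is also fair that the totals of 51, 27 and 13 replace the protocol's experimental SD of 1.3 with 4.9. They are therefore shown as an assumption beside the figures from the stated SDs. Likewise, 52 is simply 2 x 26; the protocol does not say that its 20 percent increase is for dropout.

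A reader might infer that the primary analysis will also use a two-sample test and so lose precision. The protocol names that test for the sample size only. It states no analysis method at this point, and a separate analysis plan may do so. That inference is not supported.

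**Conclusion.** The mismatch is real and plain from the protocol: a crossover by design, two independent groups by calculation. The stated 26 per group at 80% power is not a property of the within-participant comparison.

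Its size depends on r and on the contrast. With the protocol's SDs and a direct contrast, 80% power needs 18 to 29 participants in total for r from 0.8 down to 0, and 52 give 97% to 99.9%. With SD 4.9 under both treatments the range is 13 to 51, and power at 52 is 81% to above 99.9%. With changes from period baselines, power at 52 is 67% at r = 0.3 and 81% at r = 0.5. All of this assumes a two-sided 0.05 test, a difference of 2.78 and balanced sequences.

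Two stronger readings do not follow. One is that the trial is underpowered: for a direct contrast with r of 0 or more the error goes the other way. The other is that enrolment can safely be cut, or that no increase could ever be needed: the baseline-change case shows otherwise, and the protocol has no within-participant SD to settle it. The point is worth correcting before the sample-size statement is relied on, but it does not invalidate the trial.

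**What to change.** Keep the planned 64 and rewrite the sample-size paragraph so that it:

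- names the primary within-participant contrast (treatment effect adjusted for period), and says whether it compares end-of-period GPS or change from each period's baseline;
- bases the calculation on the matching SD of the difference: for end-of-period scores SD_diff = sqrt(SD1^2 + SD2^2 - 2 x r x SD1 x SD2), with a source for the SDs and a range of r (for example 0 to 0.8), using a t-based calculation because the totals are small;
- states total N and N per sequence, and the power for 2.78 and the detectable difference that 52 and 64 participants in total deliver.

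If the sponsor prefers to keep the parallel-group size as a conservative choice, one sentence saying so for the named contrast is enough, provided the figures show it is conservative for that contrast. The sample size should not be lowered without a sourced within-participant SD.

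The cost is one rewritten paragraph. Keeping 64 adds no participants and no visits.

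### The sample-size section labels the experimental-group mean (11.12) as the target difference, which is 2.78, and the stated inputs give 26.10 per group, which rounds up to 27 and not 26

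*Protocol*

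**What the plan says.** The protocol's section on the number of research participants uses a calculation to "estimate the sample size of difference two independent mean test due to a randomized controlled trial". Its inputs are:

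- error rates: "Based on Alpha error 0.05 and power of the study 0.8"; sidedness is not stated
- control mean: "Mean Gait Profile Score (GPS) of spastic cerebral palsy in the control group 13.90"
- difference between the groups: "for the alternate hypothesis was 20 percent or 11.12"
- SDs: "The standard deviation of the Gait Profile Score (GPS) of the control group was 4.9" and "Standard deviation of the Gait Profile Score (GPS) of the experimental group valued at 1.3"

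The result is: "The sample size was calculated for each group of 26 cases". The heading directly above the inclusion criteria then adds: "In case the sample size increases by 20 percent, the total sample size is 32 cases per group". The protocol does not say what the 20 percent increase is for.

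**The concern.** Two statements in this section do not agree with the section's own figures.

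First, the target difference in the primary outcome is printed as 11.12, which is 80% of the control mean and not 20% of it. The target difference is the figure a reader uses to judge whether the trial looks for a plausible effect, and it is likely to be copied into reports.

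Second, the stated inputs lead to slightly more than 26 per group, so 26 does not quite reach the stated power of 0.8. At stake is whether effect, power and number can be reproduced from the text as printed.

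**Working it through.** **Inputs.** All come from the sample-size section: control mean 13.90, SDs 4.9 and 1.3, alpha 0.05, power 0.8, two independent means, equal groups. Two-sided alpha is assumed.

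**The difference.** 13.90 × 0.20 = 2.78, and 13.90 − 2.78 = 11.12. So 11.12 is the experimental-group mean under the alternative. As a difference it is overstated by a factor of 11.12 / 2.78 = 4.

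**Reproducing the stated number.** The normal formula is n per group = (z₀.₉₇₅ + z₀.₈₀)² × (SD₁² + SD₂²) / difference².

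- (1.960 + 0.8416)² = 7.849
- 4.9² + 1.3² = 24.01 + 1.69 = 25.70
- 2.78² = 7.728
- n = 7.849 × 25.70 / 7.728 = 26.10

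This is 26 to the nearest whole number and 27 when rounded up, as a required number should be.

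**Which inputs were used.** Other readings do not come near 26:

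- one-sided alpha: 20.56, so 21
- SD of 4.9 in both groups: 49
- 11.12 taken as the difference: 7.849 × 25.70 / 11.12² = 1.63, so about 2

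The calculation therefore used a difference of 2.78 (or a close rounding of it), both SDs and two-sided alpha.

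**Power by number analysed per group,** difference 2.78, two-sided 0.05:

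| n per group | Normal | Pooled t | Unequal-variance t |
| --- | --- | --- | --- |
| 25 | 78.3% | 76.6% | 75.3% |
| 26 | 79.8% | 78.3% | 77.1% |
| 27 | 81.3% | 79.9% | 78.7% |
| 28 | 82.7% | 81.3% | 80.2% |
| 32 | 87.3% | 86.3% | 85.5% |

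For example, at 26 by the normal formula the standard error is √(25.70/26) = 0.994, 2.78/0.994 = 2.796, and Φ(2.796 − 1.960) = 0.798. The t columns use the noncentral t distribution, with 2n − 2 degrees of freedom for the pooled test and Satterthwaite degrees of freedom for the unequal-variance test. Each t test first reaches 80% at 28.

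**The 20 percent.** 26 × 1.2 = 31.2, rounded up to 32, so this step follows from the 26. If the increase were meant to cover a 20% loss, 32 × 0.8 = 25.6 would remain, slightly below 26.

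**The case against.** The strongest reply is that the number 26 is sound for practical purposes. It comes back from the protocol's inputs as 26.10, and power at 26 by the normal formula is 79.8%, which is 0.8 to the precision the protocol uses. Had the difference been rounded to 2.8, the formula would give 25.73 and 26 would be the correct rounding up. The larger shortfalls come from t tests, and the protocol names no particular variant. This stands: under the simplest method the gap is a rounding matter of one patient per group.

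The mislabelled difference is also recoverable, since the same bullet says 20 percent and the control mean stands just before it. That stands too, but it does not make the printed figure right.

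A reader might go further and infer that the trial lacks its stated power. The document does not support that, for three reasons:

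- The recruitment target is 32 per group, above both 27 and 28.
- The 20 percent is not described as a loss allowance, so no promise of 80% power after 20% loss is made or broken. The research-methods section does mention preventing loss to follow-up, but does not link it to this figure.
- All the powers above are for a parallel comparison of two groups, while the research-methods section describes a crossover in which both groups receive both treatments. As an illustration only, assume the protocol's SDs, no within-patient correlation, no carryover and all 52 patients (2 × 26) completing both periods. The standard error is then √(25.70/52) = 0.703, 2.78/0.703 = 3.95, and power is Φ(3.95 − 1.96), about 98%.

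**Conclusion.** The difference is misstated: 11.12 is a group mean and the difference is 2.78. This is certain from the protocol's own figures and needs no assumption. It is an error of labelling that did not affect the number of patients.

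The 26 is one short of the number the stated inputs require by the normal formula (27), and two short for a t test (28). Power at 26 is just under 80%: 79.8% by the normal formula and 77% to 78% by t tests. This assumes two-sided alpha, which the protocol does not state but which reproduces its figure, and takes the stated means and SDs at face value.

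The planned 32 per group gives 85% to 87% on the same basis if all are analysed. The trial should not be described as underpowered on this evidence.

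**What to change.** In the sample-size section:

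- Write the effect as: difference 2.78 (13.90 versus 11.12).
- State that alpha is two-sided, if that is what was used, and name the test.
- Either state 27 per group by the normal formula (28 if a t test is used), or keep 26 and give its power as just under 80% (77% to 80% depending on the test) for a parallel two-group comparison.

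Above the inclusion criteria, keep 32 per group and say what the increase is for. If it is a loss allowance, note that 32 less 20% is 25.6, slightly below 26. If the base number is changed, the percentage must change with it: 32 is 18.5% above 27 (5/27) and 14.3% above 28 (4/28).

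The cost is a few words. No patient is added, and the stated power or margin becomes slightly less favourable.
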